### Study population

All Danish CRC survivors above age 18 diagnosed after implementation of the CRC screening programme in March 2014 who have completed curative-intent cancer treatment with surgery and/or radiation and/or adjuvant chemotherapy will be invited to participate in the survey. Estimated number is 15,000 as the incidence is 5,000, and 80 % are offered curative intent treatment. One-year survival rate (data from 2011-2015) is 85 %. 5-year survival rate is 65 %. Overall survival rate used for this estimation is 75 %.

The RCT participants are recruited among the 15,000 colorectal cancer survivors invited to take part in survey. Through cooperation with the Danish Cancer Society we expect a slightly higher response rate than previous reported [43] of 60 %.

Among those 9,000, 12 % (1,080) are expected to score 22 or above on the FCRI-SF [13].

Approximately half of those are expected to be willing to participate in a randomised trial[37], resulting in 540 eligible participants.

The survivors will be identified through the Danish Colorectal Cancer Group (DCCG) database hosted by The Danish Clinical Registries (RKKP) with no need to enter individual patient records. The registry does not contain data on recurrence, and the cover letter will need to explain carefully, that in case of disease recurrence, the participants are asked to notify us in the first question or simply ignore the inquiry from us (see appendix 2. Følgebrev).

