### Exclusion criteria for participating in the RCT:

- Severe psychiatric or cognitive disorder identified during telephone interview

- Cancer recurrence at any follow-up
- Substance abuse

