**Part 2 b, randomization**

*If randomized to augmented TAU:* The control group is described as “augmented” as the diagnostic telephone interview exceeds standard treatment. Furthermore, if randomized to augmented TAU the information letter (appendix 7. Informationsbrev) send to E-boks will include a reference to a website with a non-guided, publicly available E-learning program in cancer rehabilitation hosted by the Region of Central Jutland (livogkraeft.rm.dk). The website includes, besides a written material, self-help instructions for meditation. Use of the website will not be monitored.

*If randomized to TG-iConquerFear:* The information letter (Appendix 7. Informationsbrev) will contain a link to enter the platform directly. The assigned therapist will be informed simultaneously.

Both groups will follow standard surveillance according to national guidelines for cancer recurrence at a surgical or oncological department, which may include colonoscopy and/or CT scans. The municipality is responsible for rehabilitation and offers limited access to physical exercise, yoga, dieticians, psychologists, sexologists etc.

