### **Part 4, intervention**

The theoretical frame of iConquerFear[29] is based on the Common-Sense Model (CSM) of illness, the Self-Regulatory Executive Function model (S-REF; targets metacognitions) and Relational Frame Theory (RFT; theoretical basis for Acceptance and Commitment Therapy). The intervention includes elements of attention training, increasing metacognitive awareness, acceptance & mindfulness, promotion of expedient screening behaviour, and values-based goal setting. The platform is accessed through secure log-on and comprises 5 modules containing educational text, interactive exercises, short videos featuring doctors, therapists and patients' perspectives, see Fig. 3.

The Australian version of iConquerFear is completely self-directed.

The Danish version of iConquerFear will contain a messenger-function on the intervention dashboard, allowing the participant and therapist to communicate asynchronously (TG-iConquerFear). The participant is guided through the sessions by minimum weekly contact with an experienced therapist. The therapist will motivate, answer questions and give feedback on written material and exercises. The amount of contact will be recorded and explored as a moderator of intervention efficacy. Should any cancer-related questions occur, an oncologist or surgeon will be involved as a consultant to the therapists.

The programme can monitor adherence, dropouts and track log-ins and activity. A purpose-developed single-item questionnaire within the TG-iConquerFear will each week ask for level of engagement[47]. Participants who do not adhere to, or withdraw from, the intervention will be contacted by telephone and asked why. These participants will be asked if they would be willing to complete a post-intervention assessment and all follow-up assessments to aid intervention evaluation. Therapist assistance is scheduled to last 10 weeks, but the participants will have free access to the platform for another 6 months.

In case of recurrence during the 10 weeks of intervention, the participant will be excluded from analysis, but may continue in the programme.

Fig. 3, iConquerFear curriculum content

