## 3. Analysis populations

- **Intention-to-treat (ITT):** All randomized participants analyzed according to their assigned group, regardless of adherence. The ITT population will form the primary analysis set.
- **Per-protocol (PP):** All participants who adhere to the intervention (>2 of 6 modules completed in TG-iConquerFear, or equivalent engagement with control condition). PP analyses will be performed to examine the robustness of ITT findings.
- **Exploratory subgroups:** Completers (6 modules) versus partial completers (2–5 modules). Analyses will also explore differences in demographic and psychosocial characteristics between subgroups.

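### The protocol drops participants with a recurrence during the 10 intervention weeks from analysis, which contradicts the SAP's all-randomised primary set; the likely numerical effect is small

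*Combined protocol and SAP*

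**What the plan says.** Three places bear on recurrence after randomisation.

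- Protocol, *Part 4, intervention*: "In case of recurrence during the 10 weeks of intervention, the participant will be excluded from analysis". The sentence goes on to let such a participant keep using the programme.
- Protocol, *Exclusion criteria for participating in the RCT*: "Cancer recurrence at any follow-up". No time limit is given, and it is not said whether the follow-up meant is cancer surveillance before enrolment or the trial's own follow-up.
- SAP section 3: "All randomized participants analyzed according to their assigned group, regardless of adherence", and "The ITT population will form the primary analysis set". The SAP nowhere mentions how recurrence is handled.

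On how recurrence would become known: Fig. 2 of the protocol marks it in the population-screening column only. Under *Study population* the protocol says of the source database: "The registry does not contain data on recurrence". At screening it is therefore self-reported.

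On contact during the 10 weeks, the intervention section says: "The participant is guided through the sessions by minimum weekly contact with an experienced therapist". For the control arm's website, Part 2 b says: "Use of the website will not be monitored". The Ethics section has the assigned psychologist register serious adverse effects, and Part 2 b describes assigning a therapist for the intervention arm only.

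**The concern.** Removing people because of something that happens after randomisation means that the groups compared are no longer the groups randomised. Here one document requires the removal and the other rules it out, so the population behind the primary result is not defined. With a revised target of 68 in total (SAP, September 2023 update), a primary comparison of mean change scores by t-test (SAP 5.2) and no imputation (SAP 6), a removed participant simply disappears from the result.

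The second worry is unequal knowledge. If the team hears of recurrences mainly through therapists, the rule could be applied more often in one arm than in the other. If those removed also had different FCRI scores from those kept, the between-group difference would move for reasons unrelated to treatment.

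**Working it through.** **Do the rules conflict?**

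| Place | Event window | Consequence |
|---|---|---|
| Protocol, Part 4 | 10 weeks of intervention | Out of the analysis |
| Protocol, RCT exclusion criteria | Any follow-up, undefined | Excluded, whether from entry or later is unclear |
| SAP 3 | Not mentioned | All randomised are analysed |

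The first and third rows cannot both be followed for a participant whose cancer recurs in week 6, say. The second row can be read as eligibility only, in which case it largely repeats the inclusion criterion of no previous recurrence. It can also be read as exclusion at any trial follow-up, which would be wider than Part 4. No text settles precedence.

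**How large could the effect be?** The plan has no figure of its own to reproduce here, because it gives no recurrence rate.

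Inputs:
- Arm size 34: the revised total of 68, split 1:1.
- Planned effect d = 3.5/7 = 0.5 (protocol *Power calculation*; SAP 2).
- Annual recurrence risk r: **assumed** 2%, 5% and 10%.
- D, the gap between removed and retained participants in SD units of the analysed score: **assumed** 1 and 2.

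Formulas: 10-week risk p = 1 − (1 − r)^(10/52). Expected cases per arm = 34 × p. If a fraction f of one arm is removed and none of the other, that arm's mean moves by f × D, and d moves by about the same amount (ignoring any small change in the SD).

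| r per year | p in 10 weeks | Cases per arm of 34 | Shift in d, D = 1 | Shift in d, D = 2 |
|---|---|---|---|---|
| 2% | 0.0039 | 0.13 | 0.004 | 0.008 |
| 5% | 0.0098 | 0.33 | 0.010 | 0.020 |
| 10% | 0.0201 | 0.68 | 0.020 | 0.040 |

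These are expected shifts. If one person is actually removed from one arm, f = 1/34 = 0.029, and d moves by 0.03 (D = 1) or 0.06 (D = 2).

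**Plausibility of larger counts.** One case in 34 within 10 weeks corresponds to 1 − (1 − 1/34)^(52/10) = 14% a year, and three cases to 1 − (1 − 3/34)^(52/10) = 38% a year. Eligible participants finished treatment by 31.12.18 without recurrence, and first inclusion was planned for October 2020, so they would be at least about 21 months past treatment. Zero or one case per arm is the more plausible outcome.

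**If the wider reading of the exclusion criterion applied.** Over one year, 34 × 0.02 to 34 × 0.10 gives 0.7 to 3.4 cases per arm. Therapist contact, the possible source of unequal knowledge, is scheduled for the first 10 weeks only.

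**The case against.** A reader might infer that removals will fall mainly on the intervention arm, that this favours the intervention, and that the bias could reach a third of the planned effect. The documents do not support that.

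- *Unequal removal.* Both arms follow the same hospital surveillance (Part 2 b), and *Process of participation* applies the 10-week period to both. The follow-up questionnaires are in an appendix that is not shown, so a recurrence item cannot be ruled out. What stands is narrower: equal surveillance equalises diagnosis, not what the trial team hears, and the visible text gives the team a regular route to that knowledge in one arm only.
- *Module 4.* Its content on threat monitoring and follow-up could lead to less checking as easily as to more, so it supports no direction.
- *Direction.* Nothing in the documents says how FCRI scores change after recurrence. Participants with recurrence may also not return questionnaires. With no imputation, they would then be missing from the t-test under either rule.
- *Size.* A bias of a third of d = 0.5 needs about three removals from 34, a gap of 2 SD and complete one-sidedness together (3/34 × 2 = 0.18). It also sets an arm of 34 against the effect size of the 350-participant design, whereas the 68-participant update rests on a larger expected effect.

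It can also be said that the SAP already makes intention-to-treat primary, and that its January 2025 list of deviations mentions no exclusion for recurrence. That is reassuring but not decisive: neither document states precedence, and silence does not show which rule was applied.

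Finally, whether a fear-of-recurrence score keeps its meaning after an actual recurrence is a fair question. It is a reason to state the handling explicitly and to run a sensitivity analysis, not to leave two rules standing.

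**Conclusion.** The contradiction is real: the protocol's intervention section removes participants for a post-randomisation event, and SAP section 3 keeps everyone randomised. The exclusion-criteria entry is ambiguous and may widen the conflict. No visible procedure identifies recurrence in the same way in both arms after screening, so more frequent detection in the intervention arm is possible but not shown, and the direction of any bias is unknown.

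The likely effect is small: an expected shift in d of no more than about 0.04, or 0.03-0.06 if one person is in fact removed from an arm of 34. These figures rest on the assumed 2-10% annual risk, the assumed gap of 1-2 SD and wholly one-sided removal. The point matters for the integrity and clear reporting of the primary analysis set rather than for the probable size of bias. It should be corrected, but ranks below the issues that must be settled before the result can be relied on.

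**What to change.** 1. Delete the analysis exclusion from the protocol's intervention section. Access to the programme after recurrence is a separate matter and is not addressed here.
2. State that the recurrence entry in the RCT exclusion criteria applies to eligibility before randomisation only.
3. State in SAP section 3 that all randomised participants, including those with a later recurrence, stay in their assigned arm for the primary analysis.
4. Report, by arm, the known recurrences, any participants already removed, and how each recurrence was identified, using the same source in both arms where one is available.
5. Confine any exclusion of post-recurrence scores to a sensitivity analysis, applied identically in both arms.

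Items 1-3 and 5 cost a few sentences and one extra analysis. Item 4 may be limited by what was collected. The Patient Registry extraction planned under *Economic measures* is a possible common source. However, the registry-based economic analysis was not undertaken, so a separate extraction might be needed, and ambulatory visits were to carry dates only, so recurrences found in outpatients could be missed. If no common source exists, the report should say so.

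The downside is that a few post-recurrence FCRI scores, whose meaning is debatable, remain in the primary analysis.

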### Process of participation

1. Receives “Følgebrev” and a survey (Spørgeskemaer, bilag 1 – screening) in E-boks.
2. Answers. Or reminded after 2 weeks
3. In case of FCRI under 22: No further participation
4. In case of FCRI at or above 22:
  - Informed of elevated level directly in the questionnaire
  - Asked if interested in hearing more about the RCT targeting FCR
  - Asked to enter phone number
  - Asked to fill out another questionnaire (45 items)
5. Telephoned by a research assistant, oral information about RCT is given (purpose, risks, benefits, voluntariness). Rescheduling in case of needing assessor.

6. Semistructured interview is performed by telephone. If possible at the same time as oral information is given, otherwise rescheduled.
7. In case of eligibility and wish to participate: Written information about RCT "Deltagerinformation", consent form "Samtykkeerklæring til projektdeltagelse" and "Før du beslutter dig"-pamphlet is send to E-boks
8. Consenting with Nem-id. Or reminded after 2 weeks of consideration.
9. No answer in 4 weeks is interpreted as not wanting to participate.
10. If consent is given: Randomization
11. Information letter "Informationsbrev" to E-boks, either with link to livogkraeft.rm.dk (control arm) or link to TG-iConquerFear (intervention arm)
12. Control arm or intervention arm for 10 weeks (Spørgeskemaer, bilag 3 – mediationsparametre)
13. 12 weeks after consent form is signed: 1st follow-up (Spørgeskemaer, bilag 4 – follow-up)
14. 12 weeks after 1st follow-up: 2nd follow-up
15. 12 weeks after 2nd follow-up: 3rd follow-up
16. 24 weeks after 3rd follow-up (One year after consent form is signed): 4th and final follow-up

## EVALUATION

### Primary outcome measure

The primary outcome measure is the 3 month follow-up (T1) total score on the recently validated Danish version of the FCRI [13]. The FCRI is a 42-item self-report measure that includes subscales assessing FCR triggers, severity, psychological distress, functioning impairments, insight, reassurance, and coping strategies [48]. The FCRI has demonstrated high: internal consistency ( $\alpha=0.96$ ) [49], interclass correlation (0.84) [13] and convergent validity in large heterogeneous cancer survivor samples. Respondents rate the degree to which symptoms/issues affected them over the past month on a Likert scale ranging from 0 ('not at all' or 'never') to 4 ('a great deal' or 'all the time'). While there are potential issues with aggregating FCRI subscales [50], total FCRI score will be used as the dependent variable, as it closely reflects proposed features of clinically significant FCR; namely related distress, functional impact, and maladaptive coping[2], rather than the level of fear indicated by the FCRI-SF [50, 51]. Total scores can range from 0-168; higher scores indicate greater FCR morbidity. Level of FCR will be measured post-treatment (T0) and at follow-up after 3 (T1) and 6 (T2) months. Long-term effect will be evaluated after one year (T3). All electronic questionnaires will be sent out automatically through RedCAP.

### Secondary outcome measures

Change from baseline (Tb) to post-intervention (T0, T1, T2, T3) in the following outcomes

- *Bodily Distress Symptom/somatization, Anxiety and depression* evaluated by relevant Symptom Checklist-90-R (SCL) subscales [52], validated in Danish by Olsen et al [53].
- *Health Anxiety* measured by the validated [54] Whiteley-8 index [55].
- *Global quality of life and global health* measured by a VAS 0-100

## Process measures

Variables likely to mediate the impact of TG-iConquerFear according to the cognitive processing and blended theoretical models of FCR and the existing research will be measured twice during the intervention and at follow-up

- *Uncertainty in illness* measured by Mishels Uncertainty of Illness Scale (MUIS) [56], validated in a short form [57]. Translated into Danish during this study.
- *Negative beliefs about worry* is a validated subscale [58] of the MetaCognitions Questionnaire-30 [59] targeting metacognition. Translated into Danish in 2009 at Center for Psychiatric Research at Aarhus University Hospital.
- *Perceived risk of recurrence* is measured by a visual analogue scale from 1-100 as presented by Lebel et al [7]. Translated into Danish during this study.

## Register data

### Baseline data

From the Danish Clinical Registries (RKKP) the following variables will be obtained prior to the RCT:

- Age
- Sex
- Participation in the Danish Colorectal Cancer Screening Program (data from the Danish Screening Database). "Yes" is annotated for individuals who submit a stool sample within three months after receiving screening invitation.
- Cancer type (colon / rectum)
- TNM stage
- Localization (left side or right side)
- Date of diagnosis
- Date of surgery
- Type of surgery
- Surgery performed with curative intent
- Radical procedure (yes / no)
- In case of no surgery performed: Cause
- Stoma (no / temporary / yes)
- Performance status
- Charlson score

### Economic measures

For evaluating cost-effectiveness of TG-iConquerFear and for comparison of changes in health care usage between intervention arm and augmented TAU, information from multiple Danish registries will be extracted. Data will be obtained at end of study for the retrospective period from intervention start to final follow-up, maximum 15 months.

From the Patient Registry (LPR) the following variables will be obtained:

- Hospitalization, duration and diagnosis
- Ambulatory visits, date

From the Health Insurance Registry (SSR) the following variable will be obtained:

- Total cost for use of primary care physician, physiotherapist and psychologist

*From Drug Statistics Registry (LSR) the following variable will be obtained:*

- Use of psychiatric related drugs (anti-depressive drugs, anxiolytics etc.)

*From the DREAM database hosted by the ministry of employment, the following variables will be obtained:*

- Sickness absence
- Leave of absence
- Marital status (for baseline)

## STATISTICAL PLAN

### Power calculation

The sample size is calculated for the primary outcome FCR measured by the FCRI. To detect a standardised mean difference in FCR (Cohen's  $d = 0.5$ , group difference of 3,5 and a standard deviation of 7) with 90 % power and two-sided  $\alpha = 0,05$  with two-sided t-test a sample size of 246 participants is desired. With a realistic dropout of 30 %, 350 participants are required in each group, and it seems realistic to recruit this as a minimum among the estimated number of eligible participants.

### Statistical analysis

A flowchart of participants and dropouts following the CONSORT guidelines will be drawn.

STATA will be used for all statistical analyses. All statistical tests will be two-sided (level of significance = 0.05).  $\chi^2$ -tests will be performed on all follow-up data to analyse proportions of participants above or below the clinical cut-off.

The influence of the intervention will be analysed for the primary outcome and for all secondary outcomes. Linear mixed effects models will be used to analyse longitudinal differences between intervention and control group. Association with functional disorders (health anxiety and bodily distress symptom) and psychiatric disorders (anxiety and depression) will be evaluated with adjusted and unadjusted linear regressions analyses on baseline data.

### Dropout analysis

Available demographic data and psychosocial information will be compared and evaluated for participants and dropouts to assess generalizability. Any differences will be taken into account in later analyses.

### Predictor analysis

The moderating effect of age, gender and cancer-related characteristics (stage of disease (I-IV), type of surgery, screening vs. non-screening e.g.) and actual situation (time since last visit at hospital, time until next visit, stoma) will be analysed using linear regressions analyses.

### Mediator analysis

The mediators uncertainty in illness, perceived risk of recurrence and negative beliefs about worry will be analysed by regression models with possible interaction with the intervention.

### Economic analysis

Multivariate analysis will be performed to explore any difference between the intervention and control group. The economic cost of the average participant in each group will be calculated based on register data.

## DATA MANAGEMENT

The electronic data capture system RedCap will be used for data management with double data entry of paper questionnaires. Paper questionnaires will be shredded. During the study data will be processed and stored in accordance with applicable legislation (EU GDPR and the Danish Data Protection Act), using REDCap and OPEN Analyse via OPEN Odense Patient data Explorative Network, Odense University Hospital, Region of Southern Denmark.

The Research Clinic for Functional Disorders and Psychosomatics, Aarhus University Hospital has signed a data management agreement with Crystone A/B in Sweden. All personal information including name, phone number, social security number and data related to the intervention-platform are encrypted and stored on their server. The survey answers are stored at a random generated id.

When the study is finished, data will be transferred to the National Archives. Access to data is limited to listed authors by passwords. All data will be handled with confidentiality.

